## Abstract

This protocol describes a pilot randomised controlled trial that aims to assess the feasibility and acceptability of a 24-week remotely delivered home-based isometric exercise and behaviour change intervention for adults with arterial hypertension (AH) characterised as ≥140/90 mmHg by European and UK guidelines. The study will also explore the potential effects of the intervention on office and ambulatory blood pressure (BP). Seventy participants diagnosed with AH and receiving pharmacological treatment will be recruited from Newcastle upon Tyne, United Kingdom. Participants will be randomised with minimisation for sex and mean office systolic BP (≤140 mm Hg vs > 140 mm Hg) to the intervention (n = 35) or control group (n = 35). The intervention group will undergo 12 weeks of remotely supervised isometric wall squat exercises, three times per week, and will receive advice based on a leaflet that follows UK recommendations for behaviour change, including weight management, diet, physical activity, salt intake, alcohol reduction, and smoking cessation. After that, they will be followed for an additional 12 weeks and will continue to receive further guidance to maintain the wall squat exercise and behaviour changes. The control group will receive similar advice to that of the intervention group, reinforcing the standard care recommendation. Primary outcomes for feasibility will be determined by screening, eligibility, recruitment, and retention rates at 12 and 24 weeks. Exercise adherence will be measured by the proportion of sessions completed. Behaviour change adherence will be self-reported via a questionnaire and assessed at 12 and 24 weeks. Participant acceptability will be determined through semi-structured interviews. Secondary outcomes include office and ambulatory BP measurements at baseline, 12 weeks, and 24 weeks. Findings will guide the development of a future large-scale trial to evaluate the effectiveness and cost-effectiveness of non-pharmacological hypertension management, addressing key gaps and supporting scalable, patient-centred care.

ClinicalTrials.gov Registration Number: NCT07213479

## Introduction

Arterial hypertension (AH) is a leading risk factor for cardiovascular diseases, contributing significantly to global morbidity, mortality, and economic burden [1]. Findings from the Global Burden of Disease report list AH as one of the three leading risk factors for premature death and poor health worldwide [2]. In the United Kingdom (UK), mortality from cardiovascular disease accounts for approximately 27% of all deaths in the adult population, representing more than 160,00 deaths per year, or one death every 3-minutes [3]. Moreover, cardiovascular diseases impact the UK economy, with an estimated cost of nine billion pounds per year [4].

One of the main risk factors for cardiovascular disease is AH, characterised in the UK and European Guidelines as systolic blood pressure (BP) equal to or higher than 140 mmHg and/or diastolic BP equal to or higher than 90 mmHg [5,6]. Recent data from the World Health Organisation indicated that worldwide an estimated 1.28 billion adults aged 30–79 years have AH [1]. Specifically, in the UK, approximately 30% of all adults have AH, with most not receiving effective treatment to control their BP [7]. Public Health England suggested that better detection and management of high BP could prevent more than 9,000 heart attacks and 14,000 strokes over a 3-year period [8].

Non-pharmacological strategies through lifestyle modifications have been consistently recommended as the cornerstone of therapy for the prevention and treatment of individuals with AH, as reductions in BP levels have been associated with lower cardiovascular risk and mortality [6,9]. Current guidelines for the management of AH include exercise training and lifestyle advice for modifiable risk factor changes, such as smoking cessation, reduced sodium intake and alcohol consumption [10]. Generally, exercise recommendations have focused on aerobic activities at moderate to vigorous intensity with a vast body of literature demonstrating favourable outcomes [11]. Additionally, dynamic resistance training has been recommended for individuals with AH to improve overall strength yielding similar benefits as aerobic exercise [6]. Although crucial for non-pharmacological AH management, adherence to these traditional modalities of exercise training is low due to many barriers (13), such as a lack of time (session duration of at least 30–60 minutes), costs, and accessibility (gym subscription or specialised supervision), which pose challenges for long-term adherence.

Isometric exercise, characterised by muscular contraction without movement of the surrounding joints, has emerged as an alternative method for managing and treating AH. Isometric exercise can be performed for the upper (e.g., handgrip) and lower limbs (e.g., leg extension and wall squat), offering significant advantages, including a minimal time commitment (approximately 11–20 minutes), minimal or no equipment requirements, and accessibility as instruction can be given in person or remotely. There is a growing body of research investigating the effects of isometric exercise training (IET) for BP management. A multilevel meta-review and regression analysis [12] exploring the effects of IET for pre and hypertensive individuals concluded effectiveness in reducing office BP of −7 mmHg, −4 mmHg, and – 6 mmHg for systolic, diastolic, and mean BP respectively. Furthermore, a network meta-analysis exploring the potential best exercise for BP reduction demonstrated from all modalities, leg IET, specifically the wall squat, presented the greatest reduction in office BP, with −11 and −5 mmHg for systolic and diastolic BP, respectively [13]. One possible explanation of these findings may be associated with ischemia/reperfusion muscle mass recruitment with leg IET. It may be hypothesised that large muscle mass isometric exercise (such as that involving lower limbs) may induce a more pronounced ischemia-reperfusion response due to sustained muscle contraction and higher intramuscular pressure, leading to increased sympathetic-mediated vasoconstriction during exercise and enhanced post-exercise vasodilation [14]. This process may result in a significant reduction in systemic vascular resistance. Additionally, leg IET may exert favourable effects on autonomic cardiovascular regulation, potentially enhancing parasympathetic tone and reducing sympathetic activity [15], thereby contributing to the observed reductions in BP [16].

Current evidence supports further investigation into the use of the leg IET as an alternative modality for AH. However, to advance this area of research, several important gaps in current literature must be addressed. To date, only four studies [17–20] have investigated the effects of wall squat training, primarily in normotensive, pre-hypertensive, or non-medicated stage 1 hypertensive populations as defined by NICE classification guidelines. Although these studies elicited favourable BP reductions, it remains unclear whether these findings are generalisable to individuals with established AH, who represent the population with the greatest need for effective BP management. A critical gap in research is the absence of interventions that integrate behavioural strategies aimed at promoting long-term lifestyle changes. Furthermore, prior studies have not integrated behavioural strategies to support long-term lifestyle change. Both NICE and European guidelines emphasise that individuals with AH should receive structured lifestyle advice to increase physical activity, improve diet, and reduce smoking and alcohol consumption. Such strategies not only can reduce BP but also address co-existing risk factors, including diabetes, obesity, hypercholesterolaemia, and CVD [2].

Considering these knowledge gaps, we propose a pilot study to evaluate the feasibility and acceptability of a combined intervention incorporating remotely isometric wall squat training and behavioural support advice. We will assess adherence, acceptability, and preliminary exploratory BP effects. Findings will inform the design and sample size of a fully powered, multicentre randomised controlled trial to evaluate clinical effectiveness, wider cardiometabolic outcomes, and cost-effectiveness for integration into NHS services.

## Aims of the study

### Primary aim

To determine:

Rates of participant screening, eligibility, recruitment, and retention at 12 and 24 weeks.Participant adherence to intervention (number of sessions attended and completed)Patient acceptability of the intervention through semi-structured qualitative interviews.

### Secondary aim

To assess the feasibility and acceptability of collecting clinical and ambulatory BP data, considering the perspectives of participants and Healthcare clinical professionals, as well as data collection challenges and missing data rates. Findings will inform the suitability of these measures for a future full-scale trial.

## Materials and methods

### Study design

This is a single-centred feasibility and pilot randomised controlled trial assessing a remotely supervised leg IET and behavioural change advice for individuals with AH. The Recommendations for Interventional Trials [21] (SPIRIT) flow chart and enrolment schedule, interventions, and assessments for the trial are presented in Fig 1.

**Fig 1 pone.0353111.g001:**
[figure not shown]
The recommendation of interventional trials (SPIRIT) schedule of enrolment, interventions, and assessments.

### Ethical approval and consent to participate

The study protocol was approved by the Northumbria University Ethics Committee (May 2025, Project ID: 10198), registered, and published in ClinicalTrials.gov (registration number: NCT07213479). The study will be conducted in accordance with the principles of the Declaration of Helsinki. Participants will be provided with appropriate participant information sheets designed in compliance with national guidance. They will have adequate time to consider the information, ask questions and have them answered sufficiently. Participants will be advised that participation is voluntary, and they may withdraw from the study at any time without reason or consequence. Participants who are willing to participate will be asked to sign a consent form, which will be administered by a member of the research team. A copy of the signed consent form will be retained by the investigator and stored in accordance with UK GDPR and the 2018 Data Protection Act, and a further copy will be given to the participant.

### Eligible participants

Participants will be adults (18 years or older) of both sexes recruited through social media and advertisements in the Newcastle upon Tyne area.

### Inclusion criteria

Diagnosis of AH in accordance with NICE guidelines.Under pharmacological treatment for AH with antihypertensive drug, type and dose maintained for the previous four months.Blood Pressure with values <180 and <110 mmHg for office systolic and diastolic BP, respectively.Not currently engaged in any structured or supervised exercise training programme, including resistance, aerobic, or isometric exercise, defined as planned exercise performed ≥2 times per week at moderate or greater intensity, for at least three months prior to enrolment.

### Exclusion criteria

Body mass index >35 kg/m^2^.Presence of cardiovascular disease beyond AH.Known orthopaedic, musculoskeletal, or neurological conditions that restrain isometric exercise execution.Presence of secondary AH.Inability to follow verbal instructions or complete the study protocol.

### Randomisation

Individuals who meet the study criteria and agree to participate will be randomly assigned to one of two parallel groups: (1) remotely supervised leg IET and behaviour change advice, or (2) a control group behaviour change advice and smartwatch only. Randomisation will be performed with minimisation for sex and the mean of office systolic BP (≤140 mm Hg vs > 140 mm Hg).

### Intervention

The intervention has been co-designed with Northumbria University, Healthworks Newcastle, and patients with AH. The programme consists of:

**Phase 1** (Intensive Phase, 12 weeks) – A structured, high-support period involving thrice weekly online remotely supervised leg IET and behaviour change advice in the format of a lifestyle change leaflet (co-created with patients with AH via patient and public involvement (PPI) meetings to reinforce NICE-recommended standard care [7]. Online resources for each of the behaviour change topics will be created and delivered at weekly timepoints to allow for a steady pace of information delivery. All online resources will remain available to participants throughout the study duration, allowing for multiple reviews and reinforcement of behaviour change.**Phase 2** (Maintenance Phase, 12–24 weeks) – A transition period focused on sustaining behaviour change with monthly follow-ups and continued guidance.

#### Induction session.

Participants allocated to the intervention will complete an in-person structured induction to ensure familiarity with the technology and intervention. This includes device setup (tablet or mobile phone), online platform training, and guidance on the smartwatch (Huawei Watch D2). Participants will receive an instructional booklet and participate in a test video call to reinforce the skills. Based on our previous study [22], we have included additional support for participants who may encounter challenges with digital literacy, such as difficulties accessing online platforms, internet issues, or syncing the Huawei Watch device. This support offers direct access to our research team for immediate assistance. Based on feedback from our previous PPI meeting, we will also provide tablets and internet connectivity to patients who lack access. This will reduce digital exclusion, support engagement with the intervention, and align with our commitment to equality, diversity, and inclusion.

#### Phase 1 – Intensive programme (12 weeks).

Participants in the intervention group will undergo baseline testing for training intensity prescription by completing an incremental isometric wall squat test (IIWST) [20]. The participant’s squat height position will be ascertained by establishing foot placement, vertical lower limb and trunk positions, and knee joint angles (135°, 125°, 115°, 105°, 95°) (S1 Appendix). Stage 1 of the IIWST will require participants to maintain a squat position of 135° of knee flexion for 2 minutes. Knee joint angle will be decreased by 10° in each subsequent stage until the participant reaches the end of the 95° stage or no longer maintains the knee joint angle within 5° of the target value (volitional fatigue). Once the training knee joint angle has been established, this will be recorded and used to replicate the wall squat position for the remote-based intervention.

#### Supervised exercise programme.

Each session will be delivered online and supervised by exercise professionals or Health Improvement Practitioners, consisting of 4 × 2-minute bouts of wall squat exercise with a 2-minute rest period between bouts.

Squat Position: Participant’s 5-stage wall squat position will be based on individual calculations at baseline. A squat height ruler prototype has been developed to facilitate the home-based individual wall squat height for each stage.

Recording Measurements: After each bout, participants will record: Squat height stage and Borg (CR-10) scale rating (RPE) Target Borg Scale: Bout 1: RPE 4 (target range: 3.5–4.5); Bout 2: RPE 5.5 (target range: 5–6); Bout 3: RPE 7 (target range: 6.5–7.5); Bout 4: RPE 8.5 (target range: 8–9).

Adjustments Based on RPE: If the RPE falls outside the target zone for a given bout, participants will adjust their squat height accordingly (18).

Heart Rate Monitoring: During the session, participants will use the smartwatch (Huawei Watch D2) to continuously monitor their heart rate responses, allowing us to track physiological changes during exercise and ensure participants’ safety.

#### Phase 2 – Maintenance programme (Months 12–24 weeks).

Following the intensive 12-week intervention, participants will enter a maintenance phase to sustain long-term behaviour change, as studies have shown that extended care in the form of additional contact with treatment providers (typically once or twice a month after the initial treatment) enhances the maintenance of the new lifestyle habit [26]. This phase will be characterised by monthly follow-up phone calls to: Identify barriers to sustaining healthy behaviours; provide ongoing motivation and goal reinforcement; address challenges in maintaining lifestyle changes. During this phase, participants will continue to be encouraged to perform their wall squat training (3 times per week) and to monitor their BP using the Huawei Watch D2 and regularly upload data.

#### Control group.

Participants randomised to the control group will receive the same behaviour change advice as the intervention group, in the format of a lifestyle change leaflet and online resources to reinforce NICE-recommended standard care [7]. They will also receive a smartwatch (Huawei Watch D2) to measure their physical activity and monitor their home BP (similar to the intervention group). Readings will be uploaded via a QR code or recorded in written format using a BP diary. Unlike the intervention group, participants in the control group will not receive direct supervision or ongoing feedback from the research team.

### Outcome measurements

#### Primary outcomes.

**Feasibility outcomes:** Screening, eligibility, recruitment, and retention rates at 12 and 24 weeks.

**Exercise adherence**: Measured as the proportion of prescribed wall-squat sessions completed (from participant logs and device data), as well as mean hold time, squat stage progression, and session frequency.

**Lifestyle adherence:** Assessed by a self-reported questionnaire at 12 and 24 weeks.

**Patient Acceptability:** Determined at 24 weeks through remote, semi-structured 1:1 interviews guided by Sekhon et al.’s Theoretical Framework of Acceptability [27] and the NIH Behavior Change Consortium’s Best Practices and Recommendations [28]. Interviews will continue until data saturation is reached, which is expected to occur with 13–16 participants. Topics covered will explore experience with study participation (informed consent process, time commitment), the acceptability of measures (readability, burden), and experiences, thoughts, and attitudes toward current usual care. All interviews will be audio recorded and transcribed, and these data will be analysed thematically to generate themes and outcomes.

**Focus group discussions:** Clinical exercise physiologists and healthcare clinical professionals will be invited to participate in focus group discussions at regular intervals (~6 months) during the delivery and referral pathway. We will also characterise the remote exercise and behaviour change advice by mapping health behaviour change techniques using the 93-item BCT taxonomy (BCTTv1) [29]. This step will be crucial in informing future work to optimise the intervention and improve the transparency of the intervention content, as well as identify the targeted theoretical mechanisms of action.

#### Secondary outcomes.

This study will assess the feasibility and acceptability of collecting BP data, considering the perspectives of participants and healthcare clinical professionals (Healthworks team), as well as data collection challenges and missing data rates. Findings will inform the suitability of these measures for a future full-scale trial. Assessments will be conducted at baseline (pre-randomisation), 12 weeks, and 24 weeks at Northumbria University, Newcastle upon Tyne, UK. Office BP will be measured using an Omron HEM-742 device. Participants will sit quietly for five minutes, and readings will be taken at one-minute intervals on the right arm until a difference of less than 4 mmHg is achieved between two consecutive measurements. The average measurements will be calculated to determine the office systolic and diastolic BP. Ambulatory BP will be measured using a non-invasive oscillometric device (Welch Allyn ABPM 7100 Central Blood Pressure, USA) worn on the nondominant arm, recording measurements every 15 minutes over 24 hours. Mean systolic, diastolic, and overall BP will be calculated for the full 24-hour period, as well as during awake and asleep periods. BP variability will be assessed using 24-hour standard deviation, weighted SD (SDdn), and average real variability (ARV24).

### Study power

The study will recruit a target sample of n = 70 (intervention n = 35; control n = 35) to estimate feasibility parameters (recruitment, adherence, retention, data completeness, safety) with useful precision and to provide exploratory BP effect sizes (with 95% CIs). As this is a feasibility trial, the study is not powered to test efficacy but to estimate key parameters with acceptable precision. With n = 70, the expected precision is: Retention (assume 75%): Standard error (SE) = √ [0.75 × 0.25 / 70] ≈ 0.052; 95% CI = 75% ± 10% → 65%–85%. Adherence (assume 70%): SE = √ [0.70 × 0.30 / 70] ≈ 0.055; 95% CI = 70% ± 11% → 59%–81% These confidence intervals show that with 70 participants, we can estimate retention and adherence with a margin of error of ~±10%. This is consistent with feasibility study methodology and will provide robust data to inform the design and sample size calculation for a future definitive RCT. Progression to a definitive trial will be guided by predefined traffic light criteria.

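### Adherence precision is computed on all 70 participants, although adherence to the intervention can be observed only in the 35 allocated to it

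*Protocol article*

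**What the plan says.** The Study power section sets the size and split of the trial: "The study will recruit a target sample of n = 70 (intervention n = 35; control n = 35"). It then gives an expected 95% interval for two feasibility parameters, retention and adherence. For adherence it uses a single-proportion standard error with 70 in the denominator, "Adherence (assume 70%): SE = √ [0.70 × 0.30 / 70] ≈ 0.055; 95% CI = 70% ± 11" per cent, and gives the resulting range as 59% to 81%. It closes by stating that "with 70 participants, we can estimate retention and adherence with a margin of error of ~±10" per cent.

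Other sections fix what adherence means and who can supply it:

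- **Primary aim:** "Participant adherence to intervention (number of sessions attended and completed").
- **Primary outcomes**, exercise adherence: "Measured as the proportion of prescribed wall-squat sessions completed (from participant logs and device data"), together with hold time, squat stage and session frequency.
- **Statistical plan:** intervention adherence is listed among the feasibility outcomes to be reported as counts and percentages, with 95% confidence intervals where appropriate.
- **Randomisation:** the control group is given behaviour change advice and a smartwatch, and nothing else. The Control group section lists the same package and adds that "participants in the control group will not receive direct supervision or ongoing feedback from the research team". Neither section prescribes wall-squat sessions to controls.

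**The concern.** A participant who is prescribed no sessions has no proportion of sessions completed. The 35 controls therefore carry no information about session adherence, yet the calculation counts them. It credits the trial with twice as many informative participants as the design supplies.

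This matters because the trial is explicitly not powered for efficacy. Its stated statistical purpose is to estimate feasibility parameters with acceptable precision. Adherence is a primary outcome and one of only two parameters for which precision is worked out. Someone planning the definitive trial would take from this section that adherence will be known to within about 10 points.

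There is a second, related mismatch. The formula √[p(1 − p)/n] applies to a yes/no status per participant, whereas the Primary outcomes section describes a proportion of sessions, which takes many values within each participant. No threshold turning that proportion into a yes/no status is given alongside the calculation.

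**Working it through.** **Inputs from the protocol.** Study power section: 70 participants, 35 per arm; assumed adherence 0.70; assumed retention 0.75; 95% intervals (z = 1.96).

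**1. Reproduce the stated figures** with SE = √[p(1 − p)/n] and half-width = 1.96 × SE.

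- Retention, p = 0.75, n = 70: SE = √(0.1875/70) = 0.0518; half-width 10.1 points; interval 64.9% to 85.1%. This agrees with the protocol.
- Adherence, p = 0.70, n = 70: SE = √(0.21/70) = 0.0548; half-width 10.7 points; interval 59.3% to 80.7%. This also agrees.

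The arithmetic is right for n = 70. The question is whether 70 is the right n.

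**2. Same formula, with the participants who have sessions.**

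- Adherence, p = 0.70, n = 35: SE = √(0.21/35) = 0.0775; half-width 1.96 × 0.0775 = 15.2 points; interval 54.8% to 85.2%.
- Ratio to the stated half-width: √(70/35) = 1.41.
- A Wilson interval at the same inputs is 53.5% to 82.6%, so the choice of interval method does not change the picture.

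**3. Intervention-arm size that the stated margins would need**, from n = 0.21 × (1.96/half-width)².

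- ±11 points: 66.7, so 67 participants.
- ±10 points: 80.7, so 81 participants.
- Planned: 35.

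**4. If adherence is the mean of participants' session proportions.** The half-width is t × SD/√35, with t = 2.03 on 34 degrees of freedom and √35 = 5.92. The protocol gives no SD, so the values below are assumptions.

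| Assumed between-participant SD (points) | Half-width (points) |
|---|---|
| 25 | 8.6 |
| 30 | 10.3 |
| 35 | 12.0 |

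For proportions with mean 0.70 the SD cannot exceed √(0.70 × 0.30) = 0.458. That extreme is reached only if every participant completes either all sessions or none, and it is exactly the SD implied by the yes/no formula. The ±15 of step 2 is therefore essentially the upper bound for this version of the outcome. Conversely, an SD of about 31 points on 35 participants would give roughly the stated margin: 2.03 × 31/5.92 = 10.6.

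**The case against.** **The true margin may be close to what is stated.** This is the strongest counter-argument, and it stands in part. A reader might infer that adherence will really be known only to ±15 points. The documents do not support that without a condition. For a mean session proportion, which is how the Primary outcomes section reads, ±15 is close to the worst case, and plausible SDs give margins on either side of ±11. What remains is that the stated figure was not obtained that way: it comes from a yes/no formula on participants who have no sessions, and no SD is offered that would justify it on 35.

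**Adherence might mean lifestyle adherence, which both arms could report.** Controls receive the same advice, so a questionnaire could cover all 70. However, the Study power section does not say this. The Primary aim counts adherence in sessions, the Statistical plan speaks of intervention adherence, and the lifestyle questionnaire has no percentage or threshold to which an assumed 70% could refer. If lifestyle adherence was intended, session adherence has no precision statement, and the text still needs correcting.

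**The sample size does not rest on adherence alone.** This is correct. Retention precision properly uses 70, and the section also cites exploratory blood pressure effect sizes. It would be wrong to conclude that the rationale for 70 collapses.

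**The progression decision.** A reader might infer that the error distorts the go/no-go rule. The article mentions predefined traffic light criteria but does not list them or say that adherence is among them, so no such claim can be made.

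**Dropout.** One could argue for a still wider interval by counting only retained intervention participants. The outcome is defined on prescribed sessions, so sessions missed after withdrawal could simply count as not completed. The documents do not require a smaller denominator.

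**Conclusion.** The concern holds as a wrong denominator in a published calculation. Adherence to the intervention is observable in 35 participants, not 70. Under the protocol's own yes/no formula and its assumed 70%, the 95% interval is 55% to 85% (±15 points) instead of 59% to 81% (±11 points), which is 1.41 times as wide. The joint statement of about ±10% stands for retention and is unsupported for adherence.

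The denominator finding depends only on reading adherence as the Primary aim, Primary outcomes and Statistical plan sections describe it. The ±15 figure depends in addition on adherence being a yes/no status per participant. If it is a mean of session proportions, the margin is unknown until an SD is assumed. The planned recruitment and the descriptive analysis are unaffected, since the reported interval will come from the observed data.

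**What to change.** 1. In the Study power section, state which adherence measure is meant and that its precision rests on the 35 intervention participants.
2. Use the formula that matches the measure:
   - If adherence is a yes/no status per participant, state the threshold and give SE 0.077, 95% interval 55% to 85%.
   - If adherence is the mean of participants' session proportions, replace the binomial formula with t × SD/√35 and state the assumed SD. An SD of 25 to 35 points gives about ±9 to ±12 points.
3. Split the closing sentence: retention to within about ±10 points on 70 participants; adherence on 35 participants, to within about ±15 points under the yes/no definition, or the margin from the stated SD under the mean definition.

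The cost is wording and, under the yes/no definition, a less favourable stated precision. No additional participants are needed, and retention precision continues to support the target of 70.
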